### Study timeline

The study will start with a baseline period of 3 months during which data on door opening and noise levels will be collected in the 30 ORs included (Fig. 2). The intervention period will last 6 months per centre. The centres will be included in two successive phases: a first phase including 15 centres (7 in the intervention arm and 8 in the control arm) and the 15 remaining centres in a second phase (8 in the intervention arm and 7 in the control arm). These two phases will be separated by a baseline period of 3 months (Fig. 2). This choice has been made for logistic reasons, to ease the installation of monitoring systems and the implementation of the intervention in a smaller group of centres. A post-intervention period of 6 months, keeping the monitoring system in place in the 30 ORs, will be used to assess the sustainability of the intervention. Due to the delay in the coding process of hospital discharge data and ICD-10 codes, we will analyse the outcomes at the end of our trial only.

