### Sample size

This multicentre interventional study will include 30 healthcare facilities (HCFs) that represent 65 ORs for orthopaedic surgery. We made the hypothesis of a difference of POC rates of 7% vs 10%. Considering power of 80% (alpha = 5% bilaterally), we would need to include 2706 patients if the randomisation was individual. Because this trial is cluster randomised, an inflation factor has to be applied to this sample size, taking into account the correlation between patients clustered within a common cluster. In our design, patients are embedded with surgeons who are embedded in orthopaedic centres, which are randomly allocated. For the sample size calculation, we considered clustering at the surgeon level only, based on the assumption that the inter-patient correlation is stronger at the surgeon level than at the hospital level. Thus, considering the surgeon as the unit of clustering with an intraclass correlation coefficient of 0.05 and an average number of 54.5 patients per surgeon for a 6-month period, we calculated that 183 surgeons will be required, for an overall population of 9945 patients. Therefore, randomising 30 centres each accounting for an average of 6 surgeons allows the inclusion of 9945 patients to provide the nominal power to our trial. Although only the surgeon level correlation was taken into account in the sample size calculation, the statistical analysis will take into account the more complex hierarchical structure of the design.

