### Statistical methods

#### Data analysis

The results from the statistical analyses will be reported according to the Consolidated Standards of Reporting Trials (CONSORT) statement recommendations and its extensions for cluster randomised trials and for non-pharmacological interventions. No interim analysis will be performed. All eligible patients will be taken into account according to the initial allocation. OR, surgeon and patient characteristics will be reported using descriptive statistics. The primary outcome will be analysed using a logistic mixed model taking into account the stratification factor as a fixed effect [40]. Patients will be the unit of analysis and will be considered embedded with surgeons who will themselves be considered embedded in orthopaedic centres. Adjusted analyses may also be performed, notably in the case of baseline imbalance, a situation often encountered in cluster randomised trials, notably due to a limited number of randomisation units. A sensitivity analysis may also be planned depending on the results observed as regard to the adherence to the intervention. Intraclass correlation will be estimated within each group.

For secondary outcomes, components of the primary outcome will be analysed with an equivalent method as for the main criteria. The frequency of doors opening will be analysed with a mixed effect Poisson regression model with the duration of procedure as offset. The duration of hospital stay and the surgical intervention duration (from wound incision to closure) will be analysed using a mixed linear model after application of a Box-Cox transformation if necessary.

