Hospital discharge and ICD-10 databases will be quarterly extracted from centres and stored on a dedicated server (Hestia) housed at the Nantes University Hospital, after automatic encryption of the patient ID number. The merging of these databases with the procedures and behavioral databases will be performed using the encrypted patient ID number as the key variable (Fig. 3). Finally, the encoded, linked, national administrative healthcare databases will be stored on the dedicated server housed at the Nantes University Hospital (see the “Data collection” section).

We received ethics approval from the “Nantes University Hospital, Groupe Nantais d’Ethique dans le Domaine de la Santé” to conduct the intervention. We obtained ethics approval from the “Comité National Informatique et Liberté” to obtain encoded baseline and outcome data on patients. “Comité National Informatique et Liberté” provides approval for research projects using the collection, storage, and use of hospital databases.

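### The stated primary model uses no baseline complication rate, although a 3-month pre-intervention period and routine discharge data should make one available at little cost

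*Protocol article*

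**What the plan says.** On the baseline quarter, the Study timeline section says: "The study will start with a baseline period of 3 months during which data on door opening and noise levels will be collected". Each centre then has a 6-month intervention period, with 15 centres per arm over two phases.

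On the outcome source, the Outcomes and Data collection and management sections take POC from local and national discharge databases by algorithm. The Discussion describes this collection as passive. The section on consent, confidentiality and access to data adds: "Hospital discharge and ICD-10 databases will be quarterly extracted from centres". It gives no calendar window for these extractions.

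On the analysis, the Data analysis section says: "The primary outcome will be analysed using a logistic mixed model taking into account the stratification factor as a fixed effect". Patients are nested in surgeons and surgeons in centres. Adjusted analyses are mentioned only as a possibility, chiefly if baseline imbalance appears, and no covariate is named.

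The Sample size section uses an "intraclass correlation coefficient of 0.05 and an average number of 54.5 patients per surgeon for a 6-month period" and leaves out any further centre-level correlation.

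**The concern.** With 30 randomised units, the precision of the arm comparison depends largely on how much centres and their surgeons differ for reasons unrelated to the intervention. A cluster's own earlier outcome rate is usually a good predictor of its later one, so adjusting for it reduces that noise. Here the earlier rate should be obtainable by the linkage already planned. The sensor data are to be cut from incision to closure, so baseline procedures probably have to be identified anyway.

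Two further points favour using it. The Data analysis section itself notes that imbalance is common when few units are randomised. The Discussion concedes that differential misclassification cannot be fully excluded. A stable difference between centres in coding completeness can fall unevenly between 15 and 15 centres by chance. A baseline rate from the same coders and algorithm would adjust for part of that. It would not correct a change in coding brought about by the intervention.

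**Working it through.** **Inputs from the Sample size section.** POC 7% v 10%; power 80%; two-sided alpha 5%; surgeon ICC 0.05; m = 54.5 patients per surgeon in 6 months; 9945 patients; 30 centres.

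**The plan's own figures.**
- Individual randomisation, unpooled variance: (1.960 + 0.842)² × (0.07×0.93 + 0.10×0.90) / 0.03² = 7.849 × 0.1551 / 0.0009 = 1352.6. That is 1353 per arm, 2706 in all, as stated.
- Design effect: 1 + 53.5 × 0.05 = 3.675. Then 2706 × 3.675 = 9944.6, so 9945; and 9945 / 54.5 = 182.5, so 183 surgeons.
- All three figures reproduce. Power is 80% by the normal approximation and 77% with a t reference on 27 df.

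**Derived.** Per centre: k = 9945 / 54.5 / 30 = 6.08 surgeons and 9945 / 30 = 331.5 patients in 6 months. At constant volume that is about 166 patients in the 3-month baseline.

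**Assumed, because the documents give neither.** Hospital ICC ρc of 0, 0.005 or 0.01; between-period autocorrelation (CAC) of 0.5, 0.6 or 0.8.

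**Formulas.**
- Design effect without baseline: DE = 1 + (m − 1)×0.05 + (k − 1)×m×ρc. This gives 3.675, 5.06 and 6.445.
- Shared variance of a centre mean, as a fraction of the total variance: S = ρc + (0.05 − ρc)/k.
- Sampling part: 0.95/331.5 = 0.00287 (intervention period) and 0.95/165.75 = 0.00573 (baseline).
- Correlation of baseline and intervention-period centre rates: r = CAC × S / √[(S + 0.00287)(S + 0.00573)]. If only centre effects persist, ρc replaces S in the numerator.
- Design effect with baseline: DE × (1 − r²). Power comes from the noncentral t on 27 df, with noncentrality 0.03 / √(0.1551 × DE / 4972.5).

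**Worked case, ρc = 0.01, CAC = 0.8.** S = 0.01 + 0.04/6.08 = 0.01658. Then r = 0.8 × 0.01658 / √(0.01944 × 0.02231) = 0.637 and r² = 0.405. DE falls from 6.445 to 3.83, and power rises from 53% to 75%.

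| Hospital ICC | No baseline | Surgeon and centre effects persist, CAC 0.5 / 0.6 / 0.8 | Only centre effects persist, CAC 0.5 / 0.6 / 0.8 |
|---|---|---|---|
| 0 | 77% | 82 / 84 / 89% | 77 / 77 / 77% |
| 0.005 | 63% | 70 / 73 / 82% | 64 / 65 / 66% |
| 0.01 | 53% | 60 / 64 / 75% | 56 / 57 / 60% |

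Outside that range, with both effects persisting at hospital ICC 0.01, a CAC of 0.3 gives 56%. Perfect stability (CAC 1) gives 92% and is only an upper bound. Using 25 df, to allow for the two stratification terms, changes these results by less than one point.

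**The case against.** The strongest reply is that nothing here is wrong. A comparison of intervention-period outcomes by a logistic mixed model with surgeons nested in centres is valid for a parallel cluster trial, and leaving out a precision covariate does not bias it. That stands.

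A reader might infer that baseline complications will go unused. The text does not support this. It names door and noise data for the baseline quarter but never says that only these are collected, and it excludes nothing. The schedule and data-source figures are not shown, an analysis plan may exist, and covariates for adjusted analyses are often left to it. What remains is that the article does state the primary model, with no baseline POC in it. An unspecified analysis triggered by observed imbalance is no substitute for a prespecified covariate.

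A reader might also infer that the trial has lost power and that a baseline would recover most of it. The protocol plans for 80%. The 63% and 53% starting points come from an assumed hospital ICC, which is a separate question. The gain does not depend on it, however: it also appears at hospital ICC 0 if surgeon effects persist.

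A third inference would be that the baseline removes stable differences between centres. No between-period correlation is given, and an ICC says nothing about persistence. At hospital ICC 0.01 and CAC 0.6 the variance falls by only 23% (r = 0.478, r² = 0.228). If surgeons or their caseloads change between periods, the gain shrinks towards the last column of the table.

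**Conclusion.** The point holds as a recommended improvement to the stated primary analysis, not as an error or contradiction. The protocol has a pre-intervention quarter, an outcome source that should cover it, and a primary model that does not name it.

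The likely gain is about 5 to 22 percentage points of power. This assumes surgeon ICC 0.05, hospital ICC 0 to 0.01, CAC 0.5 to 0.8 for both surgeon and centre effects, constant volume and a centre-mean approximation. If only centre effects carry over, the gain runs from nothing (hospital ICC 0) to about 7 points (hospital ICC 0.01, CAC 0.8). The documents do not settle which case applies.

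**What to change.** Extract POC for all eligible procedures in each centre's baseline quarter, with the same algorithm and follow-up windows. Then prespecify one of the following in the primary model, before outcomes are seen by arm:

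- **Covariate.** Add the centre's baseline POC rate and, where possible, the surgeon's. A surgeon has about 27 baseline patients (54.5 / 2), so about 2.7 events at a 10% rate. Raw surgeon log-odds will therefore be unstable and sometimes undefined.
- **Joint model of both periods.** Use surgeon-within-centre random effects with period-specific components at both levels. Constrain the arm means to be equal at baseline only if baseline conduct cannot have been affected by allocation. The text does not say when centres learn their arm relative to the baseline quarter, so this should be stated. The covariate option needs the same check.

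State the hospital ICC and between-period correlation assumed.

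The cost is one more quarter in an existing extraction, one or a few extra parameters, and confirmation that the data approval covers baseline-quarter patients. Outcomes are analysed only at the end of the trial, so the timetable should not change.

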**Fig. 2 Fig2:**
[figure not shown]
Trial schedule of enrolment, interventions, and assessments (as recommended by Standard Protocol Items: Recommendations for Interventional Trials (SPIRIT) Additional file 1)

### Sample size

This multicentre interventional study will include 30 healthcare facilities (HCFs) that represent 65 ORs for orthopaedic surgery. We made the hypothesis of a difference of POC rates of 7% vs 10%. Considering power of 80% (alpha = 5% bilaterally), we would need to include 2706 patients if the randomisation was individual. Because this trial is cluster randomised, an inflation factor has to be applied to this sample size, taking into account the correlation between patients clustered within a common cluster. In our design, patients are embedded with surgeons who are embedded in orthopaedic centres, which are randomly allocated. For the sample size calculation, we considered clustering at the surgeon level only, based on the assumption that the inter-patient correlation is stronger at the surgeon level than at the hospital level. Thus, considering the surgeon as the unit of clustering with an intraclass correlation coefficient of 0.05 and an average number of 54.5 patients per surgeon for a 6-month period, we calculated that 183 surgeons will be required, for an overall population of 9945 patients. Therefore, randomising 30 centres each accounting for an average of 6 surgeons allows the inclusion of 9945 patients to provide the nominal power to our trial. Although only the surgeon level correlation was taken into account in the sample size calculation, the statistical analysis will take into account the more complex hierarchical structure of the design.

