### Trial design

This parallel-group, cluster randomised, controlled trial is designed to evaluate the superiority of a multimodal intervention (monitoring and feedback of behavioural data combined with an adaptive improvement approach) compared with routine practice. The hospital will be the randomisation unit. Cluster randomisation will be used because of the non-individual level of the intervention. Indeed, the intervention applies at the surgical-team level based on group behaviour. An individual randomisation would have been a source of group contamination. Although the intervention applies at the surgical-team level, randomising surgeons was not desirable since other team members, who work with different surgeons, would have also been a source of contamination. In the end, randomisation will be performed at the hospital level, but the surgeon will be the unit of clustering in the statistical analysis as described below. We used the Standard Protocol Items Recommendations for Interventional Trials (SPIRIT) Checklist to guide the reporting of our protocol [32] and the Template for Intervention Description and Replication (TIDieR) to guide the reporting of components of our intervention [33] (Fig. 1).

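### The claimed nominal power omits correlation between patients of different surgeons in the same randomised hospital; at the protocol's surgeon ICC of 0.05, 80% needs that correlation to be zero

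*Protocol article*

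**What the plan says.** The Trial design section sets the unit of allocation: "The hospital will be the randomisation unit". It explains that surgeons were not randomised because other team members work with several of them.

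The Sample size section assumes complication rates of 7% and 10%, and continues: "Considering power of 80% (alpha = 5% bilaterally), we would need to include 2706 patients if the randomisation was individual". It inflates that number by "considering the surgeon as the unit of clustering with an intraclass correlation coefficient of 0.05 and an average number of 54.5 patients per surgeon", with the result that "we calculated that 183 surgeons will be required, for an overall population of 9945 patients". The reason for leaving out the hospital level is given as "For the sample size calculation, we considered clustering at the surgeon level only, based on the assumption that the inter-patient correlation is stronger" for patients of one surgeon than for patients of one hospital. The section concludes that "randomising 30 centres each accounting for an average of 6 surgeons allows the inclusion of 9945 patients to provide the nominal power to our trial". It acknowledges that only the surgeon-level correlation was counted and defers the fuller hierarchy to the analysis.

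The Data analysis section then specifies that hierarchy: "Patients will be the unit of analysis and will be considered embedded with surgeons who will themselves be considered embedded in orthopaedic centres". The stratification factor, hospital type, enters the model as a fixed effect. No hospital-level ICC appears anywhere in the article.

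**The concern.** In a cluster trial the variance of the treatment comparison depends on all the correlation inside the randomised unit. An inflation factor built on surgeons alone is sufficient if surgeons are randomised, or if patients of different surgeons in one hospital are uncorrelated. The first is not the design. The second is nowhere stated, and the article gives reasons to doubt it. Surgeons within a hospital share staff (Trial design). Local context, culture and systems are said to shape operating-room practice (Background). Hospital types are said to differ in organisation, staffing and recruitment (Sequence generation).

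That correlation is stronger within surgeon does not make the weaker term small, because the weaker term applies to many more pairs of patients.

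What is at stake is how a null result is interpreted. The Discussion expects the trial to confirm or disprove an effect of staff behaviour on complications. A result without significance supports the second reading only if the power is close to what is claimed.

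**Working it through.** **Inputs from the Sample size section.** Rates 10% and 7%; two-sided alpha 5%; power 80%; surgeon ICC 0.05; m = 54.5 patients per surgeon; N = 9945; 30 centres. Control conditions gives 15 control centres, so allocation is 15:15.

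**Reproducing the plan's figures.**
- Individual randomisation: (1.96 + 0.8416)² × (0.10 × 0.90 + 0.07 × 0.93) / 0.03² = 1352.6, so 1353 per arm and 2706 in total.
- Inflation: 1 + (54.5 − 1) × 0.05 = 3.675.
- Patients: 2706 × 3.675 = 9944.55, so 9945.
- Surgeons: 9945 / 54.5 = 182.5, so 183.

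All the stated figures reproduce, and they leave no spare patients.

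**Adding the hospital term.** Patients per centre: M = 9945 / 30 = 331.5. Same-surgeon partners of a given patient: 54.5 − 1 = 53.5. Same-hospital partners under other surgeons: 331.5 − 54.5 = 277. The design effect for randomised hospitals is

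DE = 1 + (m − 1)ρ_surgeon + (M − m)ρ_hospital = 1 + 53.5 ρ_surgeon + 277 ρ_hospital,

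where ρ_surgeon is the total correlation between patients of one surgeon and ρ_hospital the correlation between patients of different surgeons in one hospital. With ρ_surgeon = 0.05 the surgeon term is 2.675. A hospital correlation of 2.675 / 277 = 0.0097, about one fifth of the surgeon value and so compatible with the article's assumption, adds as much again.

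**Power at N = 9945.** Power = Φ(0.03 / √(DE × 0.1551 / 4972.5) − 1.96). The hospital ICCs are assumptions. The last column uses a noncentral t with 28 df (30 centres less 2).

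| Assumed ρ_hospital | DE | Power, normal | Power, t on 28 df |
|---|---|---|---|
| 0 | 3.675 | 80% | 77% |
| 0.001 | 3.95 | 77% | 74% |
| 0.0025 | 4.37 | 73% | 70% |
| 0.005 | 5.06 | 67% | 64% |
| 0.01 | 6.45 | 56% | 53% |
| 0.02 | 9.22 | 42% | 40% |

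With 26 df, allowing for three hospital types as fixed effects, the t figures change by less than half a point.

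**Detectable difference.** At ρ_hospital = 0.01 the difference detectable with 80% power (normal approximation) is about 10% vs 6.1%, instead of 10% vs 7%.

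**Varying the surgeon ICC as well** (normal approximation).
- Surgeon 0.03, hospital 0.0025: DE = 1 + 1.605 + 0.6925 = 3.30, power 84%.
- Surgeon 0.02, hospital 0.005: DE = 1 + 1.07 + 1.385 = 3.46, power 82%.
- Surgeon 0.01, hospital 0.01: DE = 1 + 0.535 + 2.77 = 4.31, power 74%.

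If 0.05 is instead read as a surgeon component on top of the hospital component, power is slightly lower than in the table: 64% at 0.005 and 53% at 0.01.

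**The case against.** The strongest reply is that the simplification is disclosed, the analysis fits the full hierarchy, and the shortfall rests on hospital ICCs that the article does not give.

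- *Disclosure and the three-level model.* Both are to the plan's credit, and the model addresses the validity of inference. Neither restores power, and the section still asserts nominal power after making the disclosure.
- *The ICC is assumed.* This stands, and it limits the point. A reader might infer that the trial is underpowered by design or that 80% is definitely not delivered. The documents do not show that. The surgeon ICC of 0.05 is itself a planning value, and if the true value is lower the factor of 3.675 covers some non-zero hospital ICCs, as the 84% and 82% cases show. It does not cover a hospital ICC of 0.01 with a surgeon ICC at least as large, where power is 74% or less.
- *Stratification.* This stands in part. Hospital type is a stratum and a fixed effect, so the relevant ICC is the residual one within type. Three types cannot absorb variation among hospitals of the same type.
- *Arithmetic.* A reader might infer a calculation error. There is none: every stated figure reproduces, and the fault is a missing term.
- *Number of surgeons.* A reader might set 30 × 6 = 180 against the required 183. The article calls 6 an average, and 9945 / (30 × 54.5) = 6.08, so this is rounding.
- *Degrees of freedom.* The method can be left to the analysis plan. A centre-based t reference costs only 2 to 3 points and is secondary.

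**Conclusion.** The point holds in conditional form. At the protocol's own surgeon ICC, the nominal-power claim requires a residual hospital correlation of exactly zero, and the reason given, that correlation is stronger within surgeon, does not supply that. Any positive value lowers power below 80%; the loss stays within about two points only if the value is below roughly 0.0007.

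The direction of the effect is certain for any positive hospital correlation with the surgeon ICC at 0.05. Its size cannot be fixed from the article. The tabulated powers assume equal cluster sizes and ICCs that are not in the document.

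**What to change.** In the Sample size section:

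1. Replace the inflation factor with 1 + (m − 1)ρ_surgeon + (M − m)ρ_hospital, with m = 54.5 and M = 331.5, and define both correlations, stating that ρ_hospital is residual to hospital type.
2. Restate the power, or the detectable difference, for the planned 30 centres over a stated range of both ICCs (for example hospital 0 to 0.02, with surgeon values at and below 0.05), using small-sample degrees of freedom based on the number of centres.
3. Withdraw the nominal-power statement, or qualify it as conditional on a zero hospital-level correlation at a surgeon ICC of 0.05.

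The cost is a change of wording and a short table. No added enrolment is required and trial conduct does not change. The stated power is likely to look less favourable, which is the information needed to interpret a null result.

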## Methods and analysis

### Participants, interventions and outcomes

#### Study setting

We will conduct the trial in a selection of 30 orthopaedic surgical centres delivering knee or hip arthroplasty. The study will take place in western France and the Paris area. Centres performing more than 200 knee/hip arthroplasty per year will be contacted via local infection control and health quality teams. This group of facilities will provide a representative panel of public/private settings with variable sizes and activities. The ORs from selected centres can be equipped with or without laminar airflow, and without restriction of surface or number of doors. Centres involved in similar ongoing research on behaviour change in the OR will be excluded.

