#### Patient eligibility criteria

The population will comprise patients ages 18 years or older undergoing the surgical procedure of knee or hip arthroplasty (replacement or resurfacing) as a primary, elective or urgent referral. Patients undergoing arthroplasty revision and patients with previous SSI will not be eligible. All surgical procedures will be included, whatever the age, gender, experience and position of the patient’s senior orthopaedic surgeon.

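### The sample size uses a design effect for equal surgeon caseloads with no margin, so any spread in caseload leaves 9945 patients short of the claimed 80% power

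*Protocol article*

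**What the plan says.** The Sample size section of the protocol article assumes complication rates of 10% and 7%, with a two-sided alpha of 5% and 80% power. It states that "we would need to include 2706 patients if the randomisation was individual". It then inflates for clustering by surgeon, with an intraclass correlation of 0.05 and "an average number of 54.5 patients per surgeon for a 6-month period". The result is 183 surgeons and 9945 patients. The section adds that "randomising 30 centres each accounting for an average of 6 surgeons" makes it possible to include that number, which it says gives the trial its nominal power. It mentions no allowance for unequal caseloads.

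Two other sections describe where these surgeons come from. Study setting says that the facilities will be a panel of "public/private settings with variable sizes and activities". Patient eligibility criteria admits all procedures "whatever the age, gender, experience and position" of the senior surgeon. The Data analysis section plans a logistic mixed model with patients within surgeons within centres.

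**The concern.** The usual inflation factor, 1 + (m - 1) x ICC, is exact only when every cluster has the same size m. When sizes vary around the same mean, the same total number of patients carries less information, because extra patients of a busy surgeon add little and surgeons with few patients contribute few. The design effect rises and power falls, whatever the spread.

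The article gives 54.5 as a mean and describes a setting in which about 180 surgeons could hardly all have the same caseload. If the calculation has no spare margin, the statement that 9945 patients deliver the nominal power cannot be right on the plan's own inputs. A null result would then be read as coming from a trial with 80% power when the planned power was somewhat lower.

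**Working it through.** **Inputs from the Sample size section:** rates 10% and 7%; two-sided alpha 5%; power 80%; ICC 0.05; mean caseload 54.5; 2706 patients before inflation; 183 surgeons and 9945 patients after. **Assumed, because the article gives no figure:** the CV of patients per surgeon, taken as 0.4, 0.6 and 0.8.

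**Step 1: the plan's own figures.**
- Unpooled variance term: 0.10 x 0.90 + 0.07 x 0.93 = 0.1551. Patients per arm: (1.960 + 0.842)^2 x 0.1551 / 0.03^2 = 1352.6, rounded up to 1353, so 2706 in total. This matches.
- Design effect: 1 + (54.5 - 1) x 0.05 = 3.675.
- 2706 x 3.675 = 9944.55, so 9945. 9945 / 54.5 = 182.5, so 183 surgeons. Both match.
- Power at 9945: SE = sqrt(0.1551 x 3.675 / 4972.5) = 0.01071. Phi(0.03/0.01071 - 1.96) = 80.0%.

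The figures are the equal-cluster result, with no hidden allowance.

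**Step 2: unequal caseloads under efficient weighting.** A mixed model weights each surgeon roughly by the information contributed, m / [1 + (m - 1) x 0.05]. The design effect is then 54.5 divided by the mean of that quantity over surgeons. With equal caseloads the mean is 54.5/3.675 = 14.83. For gamma-distributed caseloads with mean 54.5 it is 14.37, 13.79 and 13.01 at CVs of 0.4, 0.6 and 0.8. A closed-form approximation gives the same design effects to two decimals: 3.675 / [1 - CV^2 x L x (1 - L)], with L = 54.5/(54.5 + 19) = 0.741.

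**Step 3: the pessimistic bound.** The simple CV-inflated design effect is 1 + [(1 + CV^2) x 54.5 - 1] x 0.05. It takes no credit for the model's weighting.

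Power at 9945 patients is Phi(0.03/SE - 1.96), with SE = sqrt(0.1551 x design effect / 4972.5):

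| Assumed CV | Design effect, mixed model | Power | Design effect, simple inflation | Power |
|---|---|---|---|---|
| 0 | 3.675 | 80.0% | 3.675 | 80.0% |
| 0.4 | 3.79 | 78.8% | 4.11 | 75.5% |
| 0.6 | 3.95 | 77.1% | 4.66 | 70.2% |
| 0.8 | 4.19 | 74.7% | 5.42 | 63.6% |

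Under the mixed model the loss reaches 2 points at a CV of about 0.5.

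**Step 4: surgeons per centre.** 30 x 6 = 180 surgeons, and 180 x 54.5 = 9810 patients, against 183 and 9945. With equal caseloads, power at 9810 is 79.5%. Since 183/30 = 6.1, the printed 6 is most likely a rounded value.

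**The case against.** The strongest reply is that nothing has been miscalculated and that the effect is small. All four printed figures reproduce. The planned analysis is a mixed model, so the larger losses from simple inflation do not describe it. The effect is also smaller than the uncertainty in the ICC: at a CV of 0.6, an ICC of 0.045 instead of 0.05 gives (1 + 53.5 x 0.045)/0.927 = 3.67, which is the plan's own design effect again. The article is condensed, and the full protocol might report a caseload CV.

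Much of this stands, and it rules out several stronger readings that a reader might infer:

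- **That the plan states that surgeon caseloads vary.** It does not. It says that centres vary in size and activity, and it calls 54.5 an average. Variation between surgeons is a strong inference from this.
- **That the centre floor proves the spread.** Study setting says "Centres performing more than 200 knee/hip arthroplasty per year will be contacted", which is about 100 in 6 months, against a required mean of 9945/30 = 331.5. This compares centres, not surgeons: a centre with 100 procedures and two surgeons has 50 per surgeon, close to the mean.
- **That power falls to 70% or below.** Over this range of CV, only the pessimistic bound goes that low.
- **That the true target is 9810.** The article never states 180 surgeons or 9810 patients; both come from multiplying what is probably a rounded average.

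What does not stand is that the claim of nominal power can be left as printed. That a slightly smaller ICC would offset the loss shows that the loss is modest. It does not make the claim correct at the ICC the plan chose. Nor is this a detail left to another document: the article fixes the number, makes the claim, and its figures match the equal-cluster formula with nothing to spare.

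**Conclusion.** The concern holds in a limited form. The calculation makes no allowance for unequal surgeon caseloads and has no margin to absorb them. The direction is certain: at a fixed total and the plan's ICC of 0.05, any spread takes power below 80%. The size cannot be fixed from the article. For an efficient mixed-model analysis it is a loss of about 1 point at a CV of 0.4, 3 points at 0.6 and 5 points at 0.8.

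These figures rest on the assumed CVs, gamma-distributed caseloads and near-optimal weighting of surgeons. They also follow the plan in counting correlation at surgeon level only. The article says openly that centre-level correlation was left out of the calculation. That is a separate matter, so these are not estimates of the trial's overall power.

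This is an unstated simplifying assumption behind an unqualified claim, not an arithmetic error. It is worth correcting because the correction is cheap. The mismatch between 183 and 180 surgeons is a minor rounding point, worth about 0.5 points of power.

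**What to change.** 1. Estimate the CV of patients per surgeon over 6 months from the participating centres' existing discharge or operating-room records.
2. Replace 3.675 with a design effect that includes this CV and suits the planned mixed model.
3. Restate the power for 9945 patients over CVs of 0.4 to 0.8, in place of the statement that this number gives the nominal power. If the simple CV-inflated figures are also shown, label them as a pessimistic bound.
4. Reconcile 183 surgeons with 30 centres of 6, for example by printing 6.1 per centre. Keep 9945 as the target.

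The cost is one data query, one recalculation and a sentence or two in the Sample size section. No extra patients and no change of design are needed. The stated power becomes somewhat less favourable.
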